# Efficacy and Safety of Remote Cardiac Rehabilitation in the Recovery Phase of Cardiovascular Diseases: Protocol for a Multicenter, Nonrandomized, Single-Arm, Interventional Trial

**DOI:** 10.2196/30725

**Published:** 2021-10-04

**Keywords:** cardiac rehabilitation, remote system, e-learning, exercise capacity, rehabilitation, cardiovascular disease, monitoring system, disease prevention, cardiology

## Abstract

**Background:**

Conventional group-based outpatient cardiac rehabilitation through monitoring and center-based approaches for patients in the recovery phase has shown strong evidence for the prevention of cardiovascular diseases. However, there are some cases in which maintaining attendance of center-based cardiac rehabilitation is difficult.

**Objective:**

This study aims to ascertain the safety and efficacy of remote cardiac rehabilitation (RCR) in the recovery phase in patients with cardiovascular disease.

**Methods:**

Patients satisfying the study criteria will be recruited from multiple institutions (approximately 30) across Japan. In total, 75 patients (approximately 2 or 3 patients from each institution) are proposed to be recruited. Patients enrolled in the RCR group will be lent devices necessary for RCR (including calibrated ergometers and tablets). Patients will perform anaerobic exercise at home using ergometer for 30-40 minutes at least 3 times weekly. During exercise, an instructor will monitor the patient in real time (using interactive video tools and monitoring tools for various vital data). Moreover, educational instructions will be given 3 times weekly using e-learning methods.

**Results:**

The primary endpoint is the peak oxygen uptake 2-3 months from the start of exercise or 6-min walk test. The extracted data will be compared between RCR patients and controls without RCR.

**Conclusions:**

The establishment of the system of RCR proposed in this study will lead to the development of more extensive applications, which have been insufficient through conventional interventions.

**Trial Registration:**

University Hospital Medical Information Network—Clinical Trials Registry UMIN–CTR UMIN000042942; https://upload.umin.ac.jp/cgi-open-bin/ctr_e/ctr_view.cgi?recptno=R000048983

**International Registered Report Identifier (IRRID):**

DERR1-10.2196/30725

## Introduction

Conventional group-based outpatient cardiac rehabilitation through monitoring and center-based approaches for patients in the recovery phase has shown strong evidence for the prevention of cardiovascular diseases [1-5]. However, maintaining attendance during center-based cardiac rehabilitation is difficult with certain patients because of the distance from their home to rehabilitation sites [5-8]. Poor program adherence is a major issue because the benefits of center-based rehabilitation depend on exercise frequency to a certain extent [9]. Moreover, because of the spread of COVID-19, this form of medical care is expected to present cluster infection–related risks. Thus, nationwide restrictions have been placed on outpatient cardiac rehabilitation (OCR) for patients with cardiovascular diseases in the recovery and maintenance phases [10-12]. Consequently, treatment for patients with high-risk cardiovascular diseases has become insufficient [13]. The suspension of OCR is expected to increase the instances of rehospitalization of patients with acute myocardial infarction and heart failure. Thus, developing alternative modalities to OCR is an urgent challenge. In recent years, reports on the possibility of remote cardiac rehabilitation (RCR) have been filed sporadically overseas [13-15]. RCR consists of health care delivery similar to that of OCR, which corresponds to monitoring during exercise, education, nutritional counseling, and psychological support via telephone and digital platforms. These include the use of artificial intelligence (AI), the Internet of Things, and e-learning technologies in monitoring the vital signs of patients staying at home, simultaneously ensuring levels of safety comparable with those of in-person monitoring by specialists [16,17]. However, since only a few reports have been available, conclusive data on the benefits of RCR are lacking. This study aims to ascertain the safety and efficacy of RCR in the recovery phase among patients with cardiovascular disease. The establishment of the system proposed in this paper will not only help patients transition from OCR to home-based care but also lead to the development of more extensive applications. In fact, the results of this study might provide some suggestions to consider more efficient ways in continued rehabilitation and disease control in the maintenance stage, which have been insufficient with conventional interventions.

## Methods

### Selection of Patients for the Study

Patients satisfying the following criteria will be recruited from multiple institutions (approximately 30) certified by the Japanese Association of Cardiac Rehabilitation across Japan: (1) patients who are recommended by the attending physician to continue postdischarge cardiac rehabilitation following in-hospital treatment for diseases indicated for cardiac rehabilitation (including ischemic cardiac disease, heart failure, aortic disease, postcardiac surgeries, and peripheral arterial disease) and (2) patients who voluntarily consent to participate in this study with a complete understanding of thorough explanations provided. Conversely, the exclusion criteria are as follows: (1) patients aged under 20 years; (2) those who are deemed unsuitable to participate in this study by the attending physician; (3) those with complications contraindicated for exercise or with high exercise-induced risks (including highly advanced valve stenosis, serious heart failure equivalent to New York Heart Association [NYHA] classification IV, at risk of serious arrhythmia [including ventricular tachycardia], and serious renal/hepatic disease); (4) those with an implanted defibrillator or ventricular assist device; (5) those with reduced cognitive function; (6) those at a terminal disease stage; (7) those at term pregnancy; and (8) those who are determined by a researcher at each institution to be unable to safely undergo RCR (eg, patients living alone). In total, 75 patients (approximately 2 or 3 patients from each institution) are proposed to be recruited. Patient recruitment started in January 2021 and proceeded through March 2021. The study timeline is described in Figure 1.

**Figure 1 figure1:**
[figure not shown]
Schematic representation of the flow of remote cardiac rehabilitation in this study. CPX: Cardiopulmonary exercise test.

### RCR Protocol

This study aims to enroll approximately 75 patients introduced to RCR and compare them with patients who received OCR for the same duration as that for a historical control group. The criteria for the control group are as follows: (1) patients who are recommended by the attending physician that they continue postdischarge rehabilitation following in-hospital treatment for diseases indicated for cardiac rehabilitation and (2) those who took cardiopulmonary exercise testing or a 6-min walk test at 2-3 months after discharge.

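### The historical controls face none of the eight exclusions applied to RCR patients, and their listed criteria do not enforce receipt of outpatient rehabilitation

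*Protocol article*

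**What the plan says.** **RCR group.** Methods, Selection of Patients for the Study, requires a physician's recommendation to continue rehabilitation after discharge, plus consent. It then lists eight exclusions: (1) age under 20; (2) judged unsuitable by the attending physician; (3) "those with complications contraindicated for exercise or with high exercise-induced risks", with NYHA IV-equivalent failure and risk of serious arrhythmia among the examples; (4) "those with an implanted defibrillator or ventricular assist device"; (5) reduced cognition; (6) terminal disease; (7) term pregnancy; and (8) "those who are determined by a researcher at each institution to be unable to safely undergo RCR (eg, patients living alone").

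**Control group.** Methods, RCR Protocol, says that the study will enrol RCR patients and "compare them with patients who received OCR for the same duration as that for a historical control group". It then gives the control criteria as a list of two: "patients who are recommended by the attending physician that they continue postdischarge rehabilitation following in-hospital treatment for diseases indicated for cardiac rehabilitation", and "those who took cardiopulmonary exercise testing or a 6-min walk test at 2-3 months after discharge". No exclusion follows, and the text does not refer back to the RCR list.

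**Abstract.** The Results paragraph says that data will be "compared between RCR patients and controls without RCR" and does not mention outpatient cardiac rehabilitation (OCR).

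**Analysis.** Data Analysis names the independent-samples t test, the Mann-Whitney U test and the chi-square test. It names no adjustment, matching or restriction.

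**The concern.** A historical control comparison is credible only if the controls could themselves have entered the experimental group. Here both groups start from the same recommendation, but only one is then filtered. The filter removes patients who would be expected to have low exercise capacity, and exercise capacity is the primary outcome. Two-sample tests would attribute any resulting difference to RCR.

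The second problem is what the comparator is. A comparison with patients who attended OCR asks whether RCR can stand in for it, and the Discussion hopes to show that RCR is a valid alternative. A comparison with a mixture of attenders and non-attenders answers a different and easier question. If the extraction team works from the two numbered criteria alone, nothing in them separates the two.

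**Working it through.** **Step 1: set the two eligibility rules side by side.**

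| Requirement | RCR | Control criteria |
|---|---|---|
| Rehabilitation recommended after in-hospital treatment | yes | yes |
| Consent | yes | not stated |
| Exclusions (1) to (8) | all eight | none stated |
| Exercise test at 2-3 months | not an entry criterion (outcome visit) | required for entry |
| OCR received | not applicable | in the lead-in sentence, not in the list |

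The shared recommendation cannot stand in for the exclusions. The protocol places all eight on top of that same recommendation for RCR patients, so it expects some recommended patients to fail them.

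**Step 2: which exclusions can be applied to records.** Numbers (1) and (3) to (7) describe the patient and can be sought in a chart. Numbers (2) and (8) are judgements about joining this study or doing RCR, and no such judgement exists for a historical patient. The example within (8), living alone, is a fact that can be checked.

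**Step 3: what is already collected.** Data Collection lists birthdate, living situation, NYHA class and pacemaker placement. It does not list implanted defibrillator, assist device, cognitive function, terminal stage or OCR attendance.

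**Step 4: the plan's own sample size, for scale.** Inputs from Data Analysis: two-sided 5%, 80% power, 67 per group after a 40% drop-out allowance. No difference or SD is given, so the figure can only be solved backwards.

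- Evaluable per group: 67 × (1 − 0.40) = 40.2, about 40; in reverse, 40 / 0.60 = 66.7, rounded up to 67.
- Implied standardised difference: (1.960 + 0.842) × √(2/40) = 0.63 (0.626 by the normal approximation, 0.634 by the t test).
- If the allowance was instead n × 1.40, 48 × 1.40 = 67.2, and 48 evaluable implies about 0.57.

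The implied difference is thus roughly 0.57 to 0.63 SD. It is a reconstruction and not a figure in the plan.

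**Step 5: illustration of the one-sided filter.** Let f be the share of controls who would have failed the RCR exclusions or had no OCR, and g their deficit in SD units. Both are assumed. The spurious difference is f × g. With no true effect and n per group, the chance of a significant result favouring RCR (nominally 2.5%) comes from the noncentral t distribution with 2n − 2 degrees of freedom and noncentrality f × g × √(n/2).

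| f | g | f × g (SD) | n = 40 | n = 75 |
|---|---|---|---|---|
| 0.10 | 0.5 | 0.05 | 4.1% | 4.9% |
| 0.20 | 0.5 | 0.10 | 6.5% | 8.8% |
| 0.20 | 1.0 | 0.20 | 14.1% | 22.9% |
| 0.30 | 1.0 | 0.30 | 26.3% | 44.6% |

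A larger sample makes the error rate worse, because the shift does not shrink with n.

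**Step 6: the opposing filter.** If the testing requirement raises the control mean by h SD relative to the RCR group, the net shift is f × g − h. At f = 0.20 and g = 0.5, an h of 0.10 SD cancels it and a larger h reverses it. The document gives none of the three quantities, so the sign is not fixed.

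**The case against.** **The lead-in already defines the comparator.** The numbered criteria can be read as narrowing a population that received OCR. This stands in part. A reader might infer that patients who never attended rehabilitation are meant to qualify, but that contradicts the stated intent. Nor does the abstract contradict the Methods, because OCR patients are also without RCR. What remains is that the list sets no attendance requirement and the abstract does not supply one.

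**The direction is not shown.** A reader might infer that the comparison must favour RCR. The second control criterion keeps only people who survived, returned and could be tested, which selects fitter controls. The physician's recommendation probably also removes some patients unfit for exercise. This stands for the net direction. It is partly offset on the primary endpoint, because an RCR patient also needs the two-to-three-month test to contribute a value. For deaths it is not offset: a control must be alive to be tested, which favours the controls.

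**The size is assumption multiplied by assumption.** This stands. In addition, Setting of Endpoints speaks of comparing improvements in exercise tolerance. If change is analysed, a deficit in level does not carry over as f × g.

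**The limitation is conceded.** Strengths and Limitations accepts that background factors may not be aligned with record-based controls. It does not mention unequal eligibility, which is a choice and not an inherent feature of historical data.

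**The groups are not wholly different populations.** This is fair: the entry recommendation is shared. Living alone is only an example within exclusion (8) and is also a recorded social factor, so it is not established that such patients are absent from the RCR group.

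**Conclusion.** The point holds on the text. The control criteria state none of the eight RCR exclusions and do not make receipt of OCR a condition, and the stated analysis is unadjusted. This is a stated rule producing unequal eligibility, not detail left to a fuller document, because the article itself sets out the control criteria.

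The bias plausibly favours RCR, but its net direction and size cannot be determined from the document. The step 5 figures show only that modest contamination could matter. They rest on assumed shares and deficits, a comparison of levels, 40 or 75 evaluable per group and no opposing selection. Expressing the bias as a percentage of the design difference would go further than the documents allow, since that difference is not stated.

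**What to change.** 1. In Methods, RCR Protocol, state that exclusions (1) and (3) to (7) apply to control records, judged at the same point in the care pathway as for RCR patients.
2. For exclusion (8), carry over only the part that can be checked, living alone. Alternatively, handle living status by restriction or a sensitivity analysis. State that (2) and the rest of (8) cannot be reproduced from records.
3. Make documented OCR participation over the same two-to-three-month period an explicit third control criterion, and say what record counts as documentation.
4. Use that comparator definition in the abstract as well.

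The cost is a wording change and a filter at chart review. Age, NYHA class and living status are covered by the listed data items. Defibrillator or assist device, cognition, terminal stage and OCR attendance are not, and need extra extraction. The control pool will be smaller. No enrolled RCR patient is affected. The change should be made before control records are selected.

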### Setting of Endpoints

The primary endpoint is the peak oxygen uptake 2-3 months from the start of exercise or 6-min walk test. The secondary endpoints are as follows: indices of cardiopulmonary exercise testing, occurrence rates of clinical events (all-cause deaths, cardiovascular deaths, and cardiovascular hospitalizations), N-terminal fragment of pro–B-type natriuretic peptide (NT-pro BNP) or BNP, health-related quality of life (QOL) scores, daily activity amounts, and questionnaire results. For both groups, various data items will be collected during regular checkups at and 2-3 months after hospital discharge, and improvements in exercise tolerance (peak oxygen intake) will be compared with the occurrence rates of clinical events.

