### Data Collection

We will also collect the following data upon admission: (1) basic information such as facility name, record date, indications for cardiac rehabilitation, hospitalization date, birthdate, sex, height, weight, and social factors (ie, living alone, living with someone, and institutionalization); (2) patient background, including history of hospitalization for heart failure, underlying heart diseases (ischemic heart disease, heart failure, aortic and peripheral artery disease, valvular disorder, and congenital heart disease), concurrent diseases/complications (hypertension, diabetes, atrial fibrillation, cerebral stroke, peripheral vascular disease, chronic kidney disease, anemia, chronic obstructive pulmonary disease, and smoking); (3) treatment history (before hospitalization), including percutaneous coronary intervention, coronary artery bypass grafting, pacemaker placement, and valve surgery; (4) discharge day; (5) vital data (blood pressure and pulse rate); (6) cardiac disease severity in accordance with NYHA classification; (7) clinical laboratory data, including lymphocyte count, hemoglobin, creatinine, sodium, albumin, total bilirubin, uric acid, and BNP or NT-Pro BNP; (8) imaging data, such as electrocardiography, chest radiography, and echocardiography (including left ventricular end–diastolic diameter, left ventricular end–systolic diameter, left ventricular ejection fraction, interventricular septum width, left ventricular posterior wall width, valve lesions, transmitral flow pattern, mitral annular ring early diastole wave, left atrial volume index, and tricuspid regurgitation maximum blood velocity); (9) 6-min walk test and cardiopulmonary exercise testing; (10) questionnaires, health-related QOL scores, and sarcopenia scores; and (11) prescribed drugs. We will collect the following items 2-3 months after discharge (at an outpatient visit): (1) vital data; (2) NYHA classification; (3) clinical laboratory data; (4) imaging data; (5) 6-min walk test and cardiopulmonary exercise testing; (5) questionnaires, health-related QOL scores, and sarcopenia scores; and (6) prescribed drugs. We will also collect the following items 1 year after discharge (at an outpatient visit): all-cause deaths, cardiovascular-related deaths, and hospitalization due to cardiovascular disease (except for planned hospitalization).

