### Data Analysis

The analysis will be performed as follows: data on the primary and secondary endpoints of the RCR and control groups will be expressed as mean (SD) or median (quadrant) values. JMP software (SAS Institute) will be used for statistical analysis. Continuous variables will be analyzed using a 2-tailed independent samples *t* test and the Mann–Whitney *U* test. For categorical variables, a chi-square test will be conducted. The RCR group will be compared with the historical control group at the primary and secondary endpoints. The sample size was calculated on the basis of the following estimation. The sample size has been estimated from the data of peak oxygen consumption. A difference in peak oxygen consumption, which is considered clinically relevant, will be in accordance with that reported previously [23,24]. Setting the 2-sided significance level at 5% and power at 80%, a sample size of 67 subjects per group will be required, after allowing for a 40% drop-out rate. Considering these issues, 3 cases are planned to be assigned to each institution (total 75 cases). The level of statistical significance will be set at *P*<.05.

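### Controls qualify only if they took the 2-3 month exercise test, while RCR patients face no such condition: deaths before the test can count only against RCR, and the primary comparison sets differently selected groups side by side

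*Protocol article*

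**What the plan says.** Under RCR Protocol, the Protocol article says it will take about 75 RCR patients and "compare them with patients who received OCR for the same duration as that for a historical control group". The second control criterion admits "those who took cardiopulmonary exercise testing or a 6-min walk test at 2-3 months after discharge".

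RCR patients enter differently. Selection of Patients for the Study asks for a physician's recommendation to continue rehabilitation after discharge and for "patients who voluntarily consent to participate in this study with a complete understanding of thorough explanations provided". Nothing there depends on a later test.

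Setting of Endpoints makes peak oxygen uptake or the 6-minute walk test, at 2-3 months, the primary endpoint. It lists among the secondary endpoints "occurrence rates of clinical events (all-cause deaths, cardiovascular deaths, and cardiovascular hospitalizations". Data Collection introduces the event follow-up with "We will also collect the following items 1 year after discharge". Data Analysis compares RCR with the historical controls on primary and secondary endpoints, using t, Mann-Whitney and chi-square tests, and states that "a sample size of 67 subjects per group will be required, after allowing for a 40% drop-out rate".

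Strengths and Limitations concedes that background factors may differ and that two different tests are mixed. It does not mention that controls are selected on having been tested.

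**The concern.** Control entry is conditioned on something that happens after baseline. A historical outpatient rehabilitation patient who died, became too ill to exercise or stopped attending before the 2-3 month visit never enters the control group. An RCR patient with the same course is already enrolled.

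Two comparisons are affected. In the event comparison, the controls' time up to the test is free of death by definition, so deaths in that period can appear only in the RCR group. Safety is one of the trial's two stated aims, so this bears directly on its conclusions. In the primary comparison, controls are the test-completing part of an unknown larger group, and the RCR patients have been selected by a different process.

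This is a stated eligibility rule rather than a detail left to an analysis plan. An analysis plan could add a common start for the event clock, but it could not bring back untested controls who were never collected.

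**Working it through.** **The plan's own figure.** 40 / (1 - 0.40) = 66.7, rounded up to 67, and 67 x 0.60 = 40.2. The stated 67 per group thus fits 40 evaluable patients per group after a 40% allowance. The article gives no numerical difference or SD, so the 40 cannot be confirmed. With 75 RCR patients, a 40% loss would leave 75 x 0.60 = 45. A control cannot lack the 2-3 month test, so this allowance does not fit the control criterion. The point does not depend on the sample size.

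**Inputs for the event comparison**
- From the article: control test at m = 2 or 3 months after discharge; events to 12 months after discharge.
- Assumed: clock starts at discharge in both groups; RCR patients are at risk from discharge; same constant hazard in both groups; 1-year mortality R of 5%, 10% or 20%.

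**Share of the year that is death-free for controls:** 2/12 = 17% to 3/12 = 25%.

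**Formulas**
- Monthly hazard: h = -ln(1 - R) / 12
- RCR risk: R
- Control risk: 1 - exp(-h(12 - m))

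Example with R = 10%, m = 2: h = 0.1054 / 12 = 0.00878; control risk = 1 - exp(-0.0878) = 0.0841; ratio = 0.10 / 0.0841 = 1.19.

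| R | m | Control risk | Risk ratio RCR/control |
|---|---|---|---|
| 5% | 2 | 0.0418 | 1.195 |
| 5% | 3 | 0.0377 | 1.325 |
| 10% | 2 | 0.0841 | 1.190 |
| 10% | 3 | 0.0760 | 1.316 |
| 20% | 2 | 0.1697 | 1.179 |
| 20% | 3 | 0.1541 | 1.298 |

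The rate version is 12 / (12 - m), that is 12/10 = 1.20 and 12/9 = 1.33.

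**Sensitivity to early risk.** If the hazard before month m is k = 2 or 3 times the later one (assumed), then h = -ln(1 - R) / (12 - m + km), and the ratio runs from 1.36 (k = 2, R = 20%, m = 2) to 1.98 (k = 3, R = 5%, m = 3).

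**In counts.** At an assumed 5% mortality, 75 x 0.05 = 3.75 deaths are expected in RCR. Of these, 3.75 x 2/12 = 0.6 to 3.75 x 3/12 = 0.9 fall in the period that is closed to controls.

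**After the fix.** With both clocks starting at month m, each group has risk 1 - exp(-h(12 - m)), so the ratio is 1.0 under the same model.

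**Primary endpoint.** The net bias is the selection shift in the analysed RCR patients minus the shift in tested controls. Untested controls are not counted and the RCR analysis set is not stated, so neither term can be filled in. If RCR patients without a test are kept in the analysis and test-takers are fitter (assumed), controls are favoured. If only tested RCR patients are analysed, the two shifts may cancel, or leave a bias of either sign.

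**The case against.** Several stronger readings are tempting, and the article does not support them.

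- **A 40% loss in RCR alone.** The 40% is attached to the size per group. It is a planning allowance, not a forecast for RCR.
- **A completers-only t test.** The article names tests but no analysis set or missing-data rule. These may stand in a document not shown, so their absence is no finding.
- **A measured bias in the primary endpoint.** One could assume that 40% of RCR patients are lost and that staying correlates 0.2-0.4 with fitness. The RCR completer mean would then rise by 0.644 x 0.2 = 0.13 to 0.644 x 0.4 = 0.26 SD, against a design effect of about 0.63 SD. But that shift covers one group only, the correlations are assumed, and the 0.63 is back-solved from 40 evaluable patients per group. It does not measure the net bias.
- **All early events impossible in controls.** This holds only for death. A control could be hospitalized in month 1, be tested later and still qualify.

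Three further objections carry weight. The article does not say when the event clock starts. RCR patients enrolled after discharge would have some death-free time of their own; if entry is at month e, the rate ratio falls towards (12 - e) / (12 - m). And high-risk patients are excluded, so the distortion may be less than one death in a secondary endpoint.

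It is also fair to say that an untested control has no primary outcome to analyse. That is a reason to model who was tested. It does not justify leaving the untested uncounted. None of these objections removes the unequal entry rule.

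**Conclusion.** The point holds in this limited form. Control entry depends on surviving to, and completing, the primary endpoint assessment; RCR entry does not; and the limitations section does not say so.

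For 1-year mortality, the rule alone gives a risk ratio of about 1.2-1.3 against RCR. This assumes counting from discharge, RCR patients at risk from discharge, and equal, constant hazards. It would be larger if risk is concentrated early and smaller if RCR patients enter after discharge. The absolute effect is probably a fraction of a death in 75 patients, but with so few deaths expected that is enough to colour a safety statement. Early cardiovascular hospitalizations are under-represented in controls by an unknown amount.

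For the primary endpoint, the groups are selected by different processes, and neither the size nor the direction of the bias can be determined from the document.

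**What to change.** 1. **Events.** Start the clock in both groups at the 2-3 month test and report earlier RCR events separately. Alternatively, follow all eligible controls from discharge, tested or not. The first option removes the death-free period but leaves controls selected on being tested; the second removes both.
2. **Control identification.** Draw controls from existing records by their eligibility at discharge. Report how many were untested and, where the records show it, how many of these had died.
3. **Primary endpoint.** Add a sensitivity analysis weighted by the inverse probability of being tested, built on the baseline items listed under Data Collection.
4. **Limitations.** State the selection on test completion next to the background imbalance already conceded.

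The controls are historical and come from clinical records, so no new procedures are needed. The costs are extra chart review for untested controls, wider intervals by an amount that depends on how many there are, and a missing-at-random assumption in the weighted analysis that the data cannot test. The landmark option also gives up any between-group comparison of the first 2-3 months.
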